### 3.6.2. Independent variables

- Socio-Demographic characteristics: Maternal age, educational level, occupation, household size, household income, and status of women in the households.
- Obstetric factors like; inter-birth interval, gestational age, parity, gravidity, abortion, and other pregnancy-related complications.

## 3.7. Timing and outputs of fieldwork

### 3.7.1. Preparatory phase

The duration of the intervention will be nine months. It will be started from Augest 2020 through December 2021. In this phase, training of counselors (midwife/Nurse) from each nearby health center/hospital for each cluster will be done. The training will equip nutrition counselors with skills and knowledge of counseling on the below-selected topics of sessions. In the same way, one community development agent per cluster will be trained to support pregnant mothers. The training of the development agent will cover topics about home garden vegetables land preparations, watering; weed control, cultivating, pest control, and disease control. It will be given for seven days by agricultural experts. In addition to the above activities, a community-based survey of first-trimester pregnant women (missed two periods) in the selected clusters/ kebeles/ will be done by health extension workers is also part of this phase.

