## 3.4. Sample Size Determinations

The sample size was estimated by G power version 3.1.9.7. Assumptions used to calculate the required sample size were: precision of 5%, power of 80%, an effect size of 0.25, and we expect a mean birth weight change of 100 gm (the primary outcome) in the intervention groups (from 2975 g to 3075 g) based on previous studies. Design effects of 2 and 15% non-response rates were also considered. The total sample size was 348 pregnant women (116 per each of the three study arms).

The sample size for each study cluster (kebele) will be allocated based on the proportion of their respective population. Accordingly, a total of eighteen clusters (kebeles) will be selected. From Mana and Seka districts eight and ten clusters (kebeles) respectively.

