## 3.5. Sampling procedures

Two districts (woreda) that could represent the two known agroecological areas of the Jimma zone will be selected. Accordingly, Mana from predominantly coffee-growing districts and Seka Chekorsa from grain and crop-growing districts were selected purposively for management and logistical reasons. Then, non-adjacent clusters or kebeles (the smallest administrative units) will be selected from both districts to have buffer zones**.** Accordingly, a total of 18 clusters (8 from Mana and 10 from Seka chekorsa) districts will be selected. Using the randomized complete block design; the clusters (kebeles) will be grouped into two blocks based on their agroecological areas (mainly coffee or grain producing). Finally, from both blocks clusters will be randomly assigned to the three study arms (husband, Peers, and control). Thus, Nase, Bidaru toli, Dimtu (of Seka), Doyo toil, Gudata bula, and Lemi Lelisa clusters(kebeles) will be assigned to the husband group. While, Siba bake, Buyo kechema, Meti, Bore, Bebela kosa, and Haro clusters will be assigned to the peer group. Likewise, Komo hare, Gepa seden, Wakito madalu, Kamise waraba, kore Lelisa, and kenteri clusters will be assigned to the control group.

Regarding the sample size allocation, it was proportionally to the population size of respective districts and kebeles (clusters). A total of 348 first-trimester pregnant women will be enrolled at baseline, 144 women will be from the mana district (48 women in each arm), and 204 women will be from the Seka-chekorsa district (68 women in each arm). This means that a total of 116 1^st^ trimester pregnant women per the three study arms will be enrolled. All of the first-trimester pregnant women who will fulfill the inclusion criteria in each cluster will be enrolled until the desired or allocated number will be achieved.

[figure not shown]

Figure 2. Map of the study area with selected study clusters (kebeles) of both districts (Seka and Mana) source: Generated using ArcGIS software version 10.3 from ETHIO-GIS, 2014 database.

Jimma zone

21 Districts ( woredas)

Goma,

Limu kosa

Mana

Gera

Gumay

Limu seka

Boter –tolay

Chora- boter

Shebe- sombo

Non benja

Omo- Nada, Omo-Beyam

Sekachekorsa

Mancho

Dedo

Kersa

Tiroafata

Sokoru,

Santama

Sigimo

Gatira

Predominantly Grain/crops producing districts.

11 districts

---

Predominantly coffee growing districts,

10 districts

Mana district selected

Mana district

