26 kebeles (clusters) total

Sekachekorsa district

37 kebeles (clusters) total

10 Clusters selected

8 Clusters selected

Coupled Intervention arm

3 clusters

Coupled intervention arm 3clusters

Mothers with their peers arm

4 clusters

Control arm

3clusters

Mothers with their peers arm

2 clusters

Control arm

3 clusters

Figure 3. Shows that the sampling procedure for the effect of home gardening and social behavioral change communication on feto-maternal outcomes in Jimma zone, South West Ethiopia, 2019.

Total=18 clusters

1. Husband intervention arm=6 clusters/kebeles (Nese, Gepa seden, Dimtu, Doyo toil, Gudata bula, Lemi lelise
2. Mothers with their peer intervention arm=6 clusters/kebeles (Siba beke, Meti,Buyo kechema, Bore,Babala kosa, Haro
3. Control arm = 6 clusters/kebeles (Bidaru tuli,Komo hare,Wakito medalu,Kemise waraba,Kore lelisa,Kenteri

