**The Home Gardening Component**

Regarding the home gardening part, the intervention groups will be provided or supplemented with four vegetable seeds (lettuce, tomato, cabbage, and carrot) which were selected by professionals consultation about the nutritious availability, and suitability to the agro-ecology of the zone, to reach for consumption (mature) within three months**.** The vegetable seeds (home garden seeds), will be supplied by identified private sector seed suppliers or farmers’ cooperatives in the respective woredas. The mother and her husband should have clearly understood that this is not mean that the pregnant mother should have to eat only in the home gardens prescribed here. But, this is just to increase the availability of various food sources in addition to what they have. Therefore, pregnant mothers should have got a variety of foods from both animals and plant sources will be given as the core message. The community development agent of the cluster will guide them from land preparation to harvest through weekly home visits. The home gardening activity should have to be done by the husband or either family members other than the pregnant mother will be remembered to avoid acquiring toxoplasma Gondi.

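### Training of counselors and garden agents is not limited to the 12 intervention clusters, so usual care in control clusters may come from staff trained on the trial's content

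*Protocol*

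**What the plan says.** Section 3.4 of the protocol states that "a total of eighteen clusters (kebeles) will be selected", and section 3.5 allocates them six to the husband arm, six to the peer arm and six to control.

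Section 3.7.1 sets up the staff. For education, "training of counselors (midwife/Nurse) from each nearby health center/hospital for each cluster will be done", and "The training will equip nutrition counselors with skills and knowledge of counseling on the below-selected topics of sessions". For gardening, "one community development agent per cluster will be trained to support pregnant mothers". No arm is named in any of these sentences. By contrast, the home gardening text in section 3.7.2 does name the arms: "the intervention groups will be provided or supplemented with four vegetable seeds".

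The personnel lines in Chapter Four cost both agent training and weekly home visits for 18 clusters.

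Section 3.7.4 says that women in all arms continue to get routine nutrition education from their antenatal providers. Section 3.7.2 places the second and third education sessions at ordinary antenatal visits. The protection against contamination described in section 3.3 is a buffer zone between clusters.

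Section 3.5 lists the clusters twice. The text reads "Komo hare, Gepa seden, Wakito madalu, Kamise waraba, kore Lelisa, and kenteri clusters will be assigned to the control group". The list under Figure 3 instead has "Control arm = 6 clusters/kebeles (Bidaru tuli,Komo hare" and "Husband intervention arm=6 clusters/kebeles (Nese, Gepa seden, Dimtu".

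**The concern.** The counselors are midwives or nurses from the facility near each cluster, and control women get their routine education from antenatal staff. If each cluster means all 18, a control woman's usual educator may have been trained on dietary diversity, extra meals, iron-folic acid and weight gain. A buffer keeps neighbors apart. It does nothing about a provider trained to serve the control cluster itself.

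If usual care in control clusters took on the session topics, knowledge, diet and possibly birth weight among controls would move toward the intervention arms and the contrast would shrink. Analysis could not repair this. A rise among controls might be visible, but the compliance measures in section 3.7.4 and Table 2 count receipt of the package and do not say that contact with trained staff is recorded in the control arm.

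**Working it through.** **1. Do the budget lines imply 18 or 12 clusters?** Inputs are from Chapter Four, Personnel costs.

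| Line | Formula | 18 clusters | 12 clusters | Difference |
|---|---|---|---|---|
| Agent training | clusters × 7 days × 300 ETB | 37,800 (as stated) | 25,200 | 12,600 |
| Home visits | 100 ETB × 38 weeks × clusters × 2 persons | 136,800 (as stated) | 91,200 | 45,600 |

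Both stated figures reproduce exactly with 18 and not with 12. The difference for the six control clusters is 12,600 + 45,600 = 58,200 ETB.

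**2. How far does that evidence reach?** It covers garden agents and an unspecified visitor. The budget has no trainee line for the midwife/nurse counselors, so their scope rests on the wording of section 3.7.1 alone. A separate line trains health extension workers for 18 clusters, but they carry out the enrolment survey, which must cover control clusters, so that line shows nothing here.

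The budget is also a loose guide to who receives what:
- Seeds are costed for 400 mothers, although the two intervention arms hold 2 × 116 = 232 women and the whole trial 348.
- The items in Table 4 sum to 258,400 + 25,200 + 116,300 + 50,200 + 123,200 = 573,300 ETB, against a stated 548,300, a gap of 25,000.
- The visit line names neither visitor nor purpose. Its weekly frequency fits the agent visits in the home gardening text but not the fortnightly agent visits in Table 2.

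**3. Upper bound on placement.** Control clusters: 6 of 18. Control women, from section 3.5: 48 in Mana + 68 in Seka Chekorsa = 116 of 348.

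**4. Would reading the text as intervention clusters only settle it?** Not fully, because the two lists in section 3.5 differ. Allowing for spelling, the peer arm is the same in both. Five control clusters are common to both: Komo hare, Wakito madalu, Kamise waraba, Kore Lelisa and Kenteri. The sixth is Gepa seden in the text and Bidaru toli under Figure 3, and the husband arm shows the reverse. If training followed one list and allocation the other, one control cluster would have trained staff and one husband-arm cluster would have none.

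**The case against.** The best reply is that section 3.7.1 is about setting up the intervention. It opens with the intervention's duration and trains counselors for the sessions, so each cluster can naturally mean each cluster where sessions are held. Seeds go to the intervention groups only, the agents then guide those same households, and the control condition is stated as routine education. The evidence is also uneven. The 18-cluster count is firmest for garden agents, who have no described contact with control women. The plausible route runs through antenatal counselors, for whom only the wording speaks.

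Much of this stands. The text is ambiguous and is not a declared decision to train control staff, and the budget is weak support. A reader might go further and infer that control women are scheduled to receive the package. The documents do not support that: no section delivers a session, seeds or an advice visit to a control woman. A reader might also turn the risk into a loss of power, but that needs a contamination rate, and the documents give none.

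What does not stand is that the meaning is obvious. The enrolment survey in the same section necessarily includes control clusters, so the section is not confined to the intervention arms. Garden-agent training is costed for 18 clusters with no stated role in a control cluster. The mismatch between the two cluster lists is a distinct defect and says nothing about whether training covers 12 or 18, but it has to be resolved before any limit to 12 has a definite meaning.

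**Conclusion.** The concern holds as a risk that the protocol leaves open. Followed literally, section 3.7.1 trains counselors and agents for control clusters too, and the buffer does not close that route. The bound is 6 of 18 clusters and 116 of 348 women; it assumes that the wording covers every cluster and counts where trained staff would be placed, not who would be exposed. The direction of any effect would be toward no difference, its size is unknown, and no loss of power is claimed. Confidence is moderate, because the counselor part depends on one sentence. The change is still worth making: it protects the main contrast, and the sponsor loses nothing by it if 12 clusters were always meant.

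**What to change.** 1. In section 3.5, make the text and the list under Figure 3 agree on the arm of Bidaru toli and Gepa seden, so that the 12 intervention clusters are fixed.
2. In section 3.7.1, limit counselor and agent training to those 12 clusters, or state that staff in control clusters are trained only after the last end-line measurement.
3. In Table 2, state that advice visits are made in the intervention arms only.
4. In Chapter Four, set agent training to 25,200 ETB and advice visits to 91,200 ETB, or state that visits in control clusters are neutral follow-up without advice.

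The cost is wording and one list correction. The two budget lines fall by up to 58,200 ETB. The drawback is less contact with control women; keeping neutral follow-up visits avoids that and uses part of the saving.

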### 3.7.2. Intervention phase

This is designed to answer the objective of the dissertation. It includes two components.

**The Social and behavioral change communication component**

This component aims to equip pregnant women and their husbands with action-oriented knowledge, behavior, and attitude that will motivate their ability to adopt optimal dietary diversity and healthcare practices for healthy feto-maternal outcomes. Different approaches to delivering education, information, and counseling techniques will be used during the secessions. Accordingly, lecture methods (direct information provision by the counselor), question and answering of unclear ideas, sharing experiences, discussions, demonstrations, telling stories, as necessary using posters, and provision of prepared leaflets will be used. At the end of each session, a summary of dietary diversity's importance to increasing the intake of nutrient-dense diets, clean drinking water, and personal and environmental hygiene importance for healthy maternal and neonatal outcomes will be a key message. Behavioral change communication (SBC) will be given three times by trained counselors. The time of delivery will be; at the begging of the intervention (during enrolment), during the second and third-trimester normal antenatal care follow-up appointments. The duration per session of education will be 1-2 hours***.***

Topics for Session 1

1. Minor disorders of pregnancy and their management.
2. Importance of dietary diversity
3. Importance of weight gain during pregnancy
4. Importance of personal and environmental hygiene
5. Importance of IFA supplementation.
6. Use of bed nets and TT vaccination
7. Importance for daytime rest during pregnancy.
8. Additional meal importance during pregnancy.
9. Importance of Iodized salt use during pregnancy.

Topics for Session 2

1. Reinforcement of the previous topics.
2. Birth preparedness and complications redness. (needs preparation for birth, place of delivery, skilled attendants for delivery, finance, transport, blood donation, emergency plan)
3. Danger signs of pregnancy that need immediate medical care.

Topics for Session 3

1. Reinforcement of previous topics.
2. Signs of Labor and delivery
3. Early and exclusive breastfeeding and colostrum
4. Institutional delivery advantages
5. Complications of the postpartum period for both (mother and neonate)

**The Home Gardening Component**

Regarding the home gardening part, the intervention groups will be provided or supplemented with four vegetable seeds (lettuce, tomato, cabbage, and carrot) which were selected by professionals consultation about the nutritious availability, and suitability to the agro-ecology of the zone, to reach for consumption (mature) within three months**.** The vegetable seeds (home garden seeds), will be supplied by identified private sector seed suppliers or farmers’ cooperatives in the respective woredas. The mother and her husband should have clearly understood that this is not mean that the pregnant mother should have to eat only in the home gardens prescribed here. But, this is just to increase the availability of various food sources in addition to what they have. Therefore, pregnant mothers should have got a variety of foods from both animals and plant sources will be given as the core message. The community development agent of the cluster will guide them from land preparation to harvest through weekly home visits. The home gardening activity should have to be done by the husband or either family members other than the pregnant mother will be remembered to avoid acquiring toxoplasma Gondi.

### 3.7.3. Monitoring and Evaluation Phase

Monitoring of intervention implementation will be carried out through supervisory visits to the study area by the principal investigator and monthly meetings with the team. It will be enhanced by recording, monitoring activities, and process evaluations. This is to confirm the progress of the interventional implementation process; whether the planned activities were implemented as scheduled, and how the pregnant mother and her family (husband) accepted and carry out the interventional activities. Also, it is for the provision of a necessary correction on time if contextual barriers will be identified during the intervention. The corrective adjustments taken during the visit will be documented. Evaluation of overall activities will be done in the middle (during late 2^nd^TMP to 3^rd^TMP) and at the last. ON

### 3.7.4. Compliance

The number of mothers who attended the health education sessions and the no. of mothers who harvest the home gardens as ordered will be followed. Also, scheduled home visits will be made by the research team to confirm the level of performance by identifying the number of mothers who comfortably attended the health education sessions and starts to carry out, the number of mothers on implementations of home gardens cultivation as guidance by the development agent. Both the intervention and control groups will receive the routine nutritional education provided by antenatal care follow-up providers as usual.

Table 2: Shows the summary of main interventional activities protocol of the effect of home gardening and social behavioral change communications on fetal outcomes in Jimma Zone, Southwest Ethiopia, 2019.

| Key action(message) | | Strategy of intervention | Responsible person | Frequency | Compliance Parameter |
| --- | --- | --- | --- | --- | --- |
| Nutritional education | Session one | Direct information provision  Sharing experiences  Discussions  Demonstrations  Telling stories  leaflets with the key message (Afan Oromo) | Trained counselors | Once during enrolment for  1-2hrs | A number of women and husbands attended nutrition education.  A number of women received the leaflet. |
|  |  |  |  |  |  |
|  | Session two | Same as above | Trained counselors | Once during the second trimester for  1-2 hours. | A number of women and husbands attended nutrition education. |
|  | Session three | Same as above | Trained counselors | Once during the third trimester for  1-2hrs hours | A number of women and husbands attended the education. |
|  | Home visiting | Provide information  Encourage  Correct | Trained counselors, peers, and PI | Monthly | The number of women visited |
| Home Gardening | Seeds provision  (lettuce, tomato, cabbage, and carrot) | Provided by preparing one teaspoon of each seed/woman. | PI and DA | Once | The number of mothers who received seeds |
|  | Land preparation and care for home gardens | Demonstrations | DA | Once | A number of women and their husbands attended the demonstrations |
|  | Home visiting | Encourage  Show  Advice  Correct | DA | Fortnight | The number of women prepared the land, planted the seeds, and used the vegetables |

*Footnote: PI; principal investigator, DA; Agricultural development agent*

## 3.8. Data collection and instruments

The data will be collected in two phases. After the home-to-the-home census of eligible pregnant mothers enrolment, the baseline data will be collected by using pre-tested structured questioners, and guidance equations. Accordingly, data on socio-demographic characteristics, obstetrics history, MUAC, Hgb level, and 24-hour recall minimum women dietary diversity scores (FAO and FHI guideline 2016) will be collected. To get the best possible information, first, the mother will be asked to narrate what she remembers followed by probes to ascertain that no meal or snack will be left out. After all, a detailed list of all the ingredients of the dishes, snacks, or other foods consumed will be generated and grouped into ten. The end-line data will be collected after the mother gave birth, just within 24 hrs.

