## 2.2. Specific objective

- 1. To measure the effect of nutritional education and home gardening interventions on minimum dietary diversity scores among pregnant women of Jimma zone.
  2. To determine the effect of nutritional education and home gardening interventions on the nutritional status among pregnant women of Jimma Zone.
  3. To determine the effect of nutritional education and home gardening interventions during pregnancy on fetal birth weight in Jimma zone.

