## 3.11. Dietary intake assessment

To determine a minimum dietary diversity score, a single point will be awarded to each food group consumed over the reference period, and a total of all points calculated. The dietary diversity will be calculated by using the minimum DD-women (MDD-W) indicator, which is an improved version of the Women's Dietary Diversity (WDD) score and has 10 food groups, consumption of at least 5 of which indicates high dietary diversity. In addition, a multiple-pass 24 hrs recall method will be used to improve memory.

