## 3.12. Anthropometric measurements

The pregnant mothers will be weighed at the begging and last ANC follow-up without shoes and with minimal or light clothing using a Seca digital scale. The readings will be taken to the nearest 0.1kg. It will be calibrated against known weight regularly. MUAC will be measured during the enrolment and at the end of the follow-up to assess wasting among the study subjects using an adult MUAC non-stretchable measuring tape to the nearest 0.1 cm. The Mid-upper arm circumference will be measured midway between the lateral projection of the acromion process of the scapula and the inferior margin of the olecranon process of the ulna.

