## 3.13. Hemoglobin level Determination

Hemoglobin will be measured at baseline and end line using a portable, battery-operated photometer (HemoCue). After swiping the site with disinfectant, a finger prick will be made to obtain blood for hemoglobin measurement. The first two drops will be swapped away and the third drop will be used to fill the micro cuvette for reading the hemoglobin. The machine will be calibrated daily with a reference microcuvette provided with the machine. A trained and skilled laboratory technologist will be responsible for the collection of blood samples and hemoglobin determination.

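### The end-line round within 24 hours after birth mixes dietary diversity and hemoglobin with peripartum effects, and weight gain is not standardised for gestational age

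*Protocol*

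**What the plan says.** Protocol section 3.8 limits data collection to a baseline and an end line: "The data will be collected in two phases". It dates the second round as follows: "The end-line data will be collected after the mother gave birth, just within 24 hrs".

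- **Diet.** The first specific objective (section 2.2) is "To measure the effect of nutritional education and home gardening interventions on minimum dietary diversity scores among pregnant women of Jimma zone". The only dietary method is a one-day recall. Section 3.8 lists it among the baseline items: "24-hour recall minimum women dietary diversity scores (FAO and FHI guideline 2016) will be collected". Section 3.11 repeats the method without dating it: "a multiple-pass 24 hrs recall method will be used to improve memory". The score is also read against a cut-off of 5 of 10 food groups.
- **Hemoglobin.** Section 3.13: "Hemoglobin will be measured at baseline and end line". Anemia is a listed dependent variable (section 3.6.1).
- **Weight.** Section 3.12: "The pregnant mothers will be weighed at the begging and last ANC follow-up". No gestational-age window is given for the second weighing.
- **Analysis.** Section 3.14 compares hemoglobin and weight gain between arms by ANOVA and adds a linear GEE, in difference-in-difference form, for birth weight and hemoglobin. It mentions neither hours since delivery nor gestational age at weighing.

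The mid-course evaluation in section 3.7.3 concerns how activities are being carried out. It is not an outcome round.

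**The concern.** The first two specific objectives concern diet and nutritional status among pregnant women. Followed as written, the schedule observes post-intervention diet only on the day around birth, and hemoglobin only after delivery. Labour, the birth and the hours after it can change what a woman eats and what her hemoglobin reads, and the plan does nothing to separate this from the effect of the intervention. Weight gain has a different weakness: a woman whose last visit falls later in pregnancy has had longer to gain, so the raw difference mixes rate of gain with date of weighing.

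At stake is the interpretation of dietary diversity, hemoglobin or anemia, and weight gain. When a measurement is taken belongs in the protocol, because no analysis plan can recover a late-pregnancy recall or hemoglobin that was never collected.

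**Working it through.** The protocol states no figure on this point, so there is nothing to reproduce. The check is window arithmetic and a comparison of sections.

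**1. Is there an end-line recall?** Section 3.8 names the recall only for baseline. The first specific objective asks for an intervention effect on dietary diversity, and end line is the only round after the intervention starts. Either the recall is repeated there, or that objective has no post-intervention data. Repetition is an inference, but the only one under which the objective can be met.

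**2. Which hours does it cover?** A 24-hour recall taken t hours after birth, with t between 0 and 24 (section 3.8), runs from (24 − t) hours before birth to t hours after it. The share before birth is (24 − t)/24.

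| t (hours after birth) | Window relative to birth | Share before birth |
|---|---|---|
| 0 | −24 h to 0 | 100% |
| 6 | −18 h to +6 h | 75% |
| 12 | −12 h to +12 h | 50% |
| 18 | −6 h to +18 h | 25% |
| 24 | 0 to +24 h | 0% |

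Every permitted recall contains or touches the birth. None reaches further back than the final 24 hours before it. Two women with the same diet in pregnancy can be scored on quite different mixtures of hours.

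**3. Hemoglobin.** Write the end-line value as H + D, where H is the late-pregnancy level and D the change around delivery.

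- If D has the same mean δ in every arm, the difference-in-difference between intervention (I) and control (C) is (H_I + δ − B_I) − (H_C + δ − B_C) = (H_I − B_I) − (H_C − B_C), where B is baseline. The common shift cancels.
- Variation of D between women does not cancel. If D is independent of H, the end-line variance rises from Var(H) to Var(H) + Var(D).
- A common shift need not cancel for a proportion below a cut-off. With F the distribution of H, anemia at cut-off c has prevalence F(c − δ), and F_I(c − δ) − F_C(c − δ) generally differs from F_I(c) − F_C(c). The same reasoning applies to the 5-of-10 food-group cut-off.

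**4. Weight gain.** If r is weekly gain and the last weighing differs by Δ weeks between two women or two arms, the raw gain differs by r × Δ from timing alone.

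**5. Size.** The protocol gives no value for the spread of D, for r or for Δ, so no distortion can be quantified from it. Figures in kilograms or in lost sample size would rest wholly on outside assumptions and are not offered as evidence.

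**6. Could timing differ by arm?** Under section 3.7.2, sessions two and three take place at antenatal appointments, and session three promotes giving birth in a facility. The date of the last visit, the place of birth, and hence food and care around the birth could therefore differ by arm. No passage shows that they do.

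**The case against.** A reader might infer that the maternal outcomes measure labour, delivery and visit timing and not pregnancy at all. The documents do not support that.

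- Arm circumference and knowledge, attitude and practice are also maternal outcomes (section 3.6.1), and nothing shows that either is spoiled by this timing.
- A recall taken soon after birth lies mostly before it. How far those hours depart from an ordinary day depends on labour duration and eating patterns, which the protocol does not give.
- Hemoglobin and the last antenatal weight still carry information about pregnancy.

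A reader might also infer bias between arms. The timing rule is the same in all arms, all arms receive routine antenatal education (section 3.7.4), the session topics do not list antenatal attendance, and the intervention also runs through home visits. A difference in visit dates is therefore conjecture. This stands: bias is an open route, not a finding.

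On weight gain, section 3.6.2 lists gestational age as an independent variable, so it is meant to be collected, and adjustment may be left to an analysis plan that is not shown. That weakens the complaint about adjustment. It does not supply a window for the second weighing, and the comparison section 3.14 names for weight gain is ANOVA.

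Finally, moving measurements to an antenatal contact relies on attendance, which may itself depend on arm, and the last visit is not at a fixed gestational age. That is a real cost of the remedy and a reason to define the window explicitly.

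The timing facts themselves are not in dispute.

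**Conclusion.** The point holds in limited form. With end line fixed within 24 hours after birth, the dietary recall always spans or touches the birth and hemoglobin is read after delivery. Both are mixed with peripartum effects when they are meant to describe diet and status in pregnancy. Weight gain is measured to an unstandardised visit.

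The case is strongest for dietary diversity, then hemoglobin and anemia, then weight gain. The expected consequence is extra noise and diluted contrasts in secondary outcomes, and comparisons at the anemia and food-group cut-offs that need not equal those in pregnancy. A common shift in mean hemoglobin cancels in the planned difference-in-difference. Bias by arm is possible but not shown, and the size is not computable from the document.

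The conclusion assumes that the recall is repeated at end line, as the first specific objective requires. Birth weight, the primary outcome (section 3.4), is unaffected. The schedule should be changed, but the point does not threaten the main comparison.

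**What to change.** - **Birth weight:** keep it within 24 hours of birth.
- **Dietary recall:** state expressly that it is repeated. Take it at the late-pregnancy contact where weight is already measured, in one gestational-age window common to all arms.
- **Hemoglobin:** take it at the same contact where the laboratory technologist can attend. If it stays after delivery, record hours since delivery and describe the result as a postpartum value.
- **Weight gain:** record gestational age at both weighings, and analyse gain per week between them or adjust for gestational age at both.
- **Arm circumference:** leave as planned; nothing here supports moving it.

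**Cost.** The weight-gain change costs almost nothing, since gestational age is already a study variable. Adding the recall to an existing contact is a small change. Moving hemoglobin costs more, because section 3.13 needs a technologist present. Chapter Four budgets two collection rounds at 67,200 ETB. If the late-pregnancy measurements had to be run as a separate third round at the same rate, that would add 67,200 / 2 = 33,600 ETB; using the existing contact should avoid part of this. Some women will miss the window, so attendance should be reported by arm. The last weeks of pregnancy will not be covered, and collection will be spread over more dates.
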